| F2.  Procedure |
| |  | | --- | | |  | Screening Interested candidates will receive an explanation of the study purpose and requirements. If still interested, the candidates will be allowed to review, inquire about, and sign the study informed consent form. After providing informed consent, subjects proceed to the screening assessment phase of the study. A urine drug toxicology screen will be conducted for drugs of abuse. Some of this sample will be shared with Rice university to develop new tests for drug detection. A saliva sample will also be collected for this purpose. Candidates deemed eligible based on initial screening assessments will be administered a MINI by a trained mental health professional, to determine if there are any psychiatric conditions that might exclude the potential subject from participation. Blood will be collected for analysis of hematology and chemistry tests. These assessments must be completed within 14 days before intake. At the initial screening visit, restrictions on use of alcohol, drugs of abuse, and medications will be reviewed. All subjects will be required to sign a written statement that they will abstain from use of cocaine or other psychostimulants throughout the duration of their participation in the trial.  All applicants for study participation will receive counseling as part of their participation, and will be advised that treatment for drug abuse is indicated and available. Applicants not participating in the study will receive treatment referral information as appropriate. At completion of their participation, study subjects will again be advised that treatment is indicated and available, and will be given treatment referral information and assistance.  Participants will reside on the Research Commons for the duration of the study (about 28 days total). Participants must refrain from illicit and prescription drug use, and we will confirm compliance by urine testing and breath alcohol level testing. Passes and monitoring. Passes will not usually be allowed, and visitors will not be permitted. Participants’ belongings will be searched upon arrival.  The study schedule outlined below may change by a day or two due to scheduling issues and/or safety reasons. We will ask participants to complete the protocol twice (once being randomized to placebo and once being randomized to doxazosin, but this wont be required.   General Procedures: Participants will be studied while residing on the Research Commons. Cocaine administration sessions will be conducted at approximately the same time of day for a given participant. Experimental sessions will be several hours in duration and will be conducted in a quiet room with research and medical staff present. The room will contain an experimental station, equipped with a response console attached to a personal computer and video monitor. Heart rate, EKG, and blood pressure will be recorded throughout experimental sessions using an automatic monitoring system.   Smoking, caffeine, and food. Caffeine and food will be prohibited during and 90 min before study sessions excepting a 1 hour break for lunch.   Day 1-10: The study participants will be randomized to receive either doxazosin or placebo. Doxazosin treatment will begin at 1mg and will be increased by 1mg increments every three days until 4mg is reached. Placebo will be dosed identically. Prior to dosing doxazosin, and at 1 hour intervals after each dose from hours 2 through 6 after dosing, sitting and supine orthostatic blood pressure will be assessed.  Cardiovascular monitoring and discontinuation criteria For doxazosin to be administered, the following criteria must be met: 1. supine blood pressure above 100/65 mm Hg, 2. a seated blood pressure of above 90/60 mm Hg, 3. and an orthostatic change smaller than 20 mm Hg systolic or smaller than 10 mm Hg diastolic on standing. The dose will not be increased until the participant has met criteria for dosing and has received 3 doses at a given dose level.  a. Participants who do not meet the criteria above at any time during hours 2 through 6 after dosing will remain supine until the next BP assessment. b. Participants who do not meet the criteria above consistently from hours 2 through 6 after any dosing will not have their dose of doxazosin increased and will remain at the prior dosing level. c. Participants who do not meet the requirements for dosing increase (supine blood pressure > 100/65 mm Hg, a seated blood pressure of > 90/60 mm Hg, and an orthostatic change < 20 mm Hg systolic or <10 mm Hg diastolic on standing) for 6 days will have medication discontinued and they will be discontinued from the study.   Day 10: Cocaine 20mg, 40mg and matched placebo saline will be administered via IV push by the study physician on day 10, at hourly intervals, with the placebo dose randomly interspersed to maintain the blind. To ensure that subjects will not be at risk from cocaine, the resting pulse must be < 90 bpm and the blood pressure must be < 150 mmHg systolic and < 90 mmHg diastolic immediately prior to dosing. Heart rate and blood pressure measurements will be made prior to cocaine dosing and at 15-minute intervals thereafter until 30 minutes following the final dose. Visual-analogue scale ratings of “any cocaine effect”, “high”, “good effects”, “bad effects”, “like cocaine”, “desire cocaine”, “depressed”, “anxious”, “stimulated”, and “if you had access to cocaine right now, how likely would you be to use it?” will be collected at -15 min, 5 min, 10 min, 15 min, 20 min, 30 min, and 45 min after cocaine dosing. Participants will remain seated during experimental sessions except for brief visits to the lavatory.   All infusions will be administered in single-blind fashion. All experimental procedures will be conducted in a hospital room located in the GCRC. Infusions will be administered over 2 minutes by I.V. push. Vital signs must remain within values specified under Stopping Criteria for initiation of cocaine administration. An ACLS-certified physician will be present from 15 min before drug administration until at least 1 hour after cocaine administration. The physician will be available in house and on pager for at least 4 hours after drug administration. Heart rate will be measured using continuous ECG from 15 min prior to cocaine or placebo dosing until 2 hours after dosing. Blood pressure will be assessed at frequent intervals from 15 min prior to cocaine or placebo dosing until 2 hours after dosing.   Discharge Participants will be monitored for stability on days 11 and 12 and discharged from the hospital on day 13. Discharge will only occur for subjects who have a supine BP of 100/65 mm Hg or higher, a seated blood pressure of 90/60 mm Hg or higher, and an orthostatic change upon standing of < 20 mm Hg systolic or < 10 mm Hg diastolic. Prior to discharge subjects will have a physical examination and vital signs, and complete the Beck Depression Inventory-II. An assessment of adverse events will be completed.  Participants will have the choice of returning two weeks later to complete study procedures.   Stopping Rules Doxazosin Participants who do not meet the criteria listed above (supine blood pressure above 100/65 mm Hg, a seated blood pressure of greater than 90/60 mm Hg, and an orthostatic change smaller than 20 mm Hg systolic or smaller than 10 mm Hg diastolic on standing) at any time during hours 2 through 6 after dosing will remain supine until the next BP assessment. Participants who do not meet the criteria above consistently from hours 2 through 6 after any dosing will not have their dose of doxazosin increased and will remain at the prior dosing level. Participants showing syncope or dizziness that does not respond to sitting down will be discharged from the study.  Stopping Criteria for Further Participation Participants who do not meet the requirements for dosing increase for 6 days will have medication discontinued and they will be discontinued from the study.  Cocaine Cocaine will not be administered if there are clinically significant arrhythmias or if vital signs are outside of acceptable ranges, which are resting pulse below 90 bpm and blood pressure below 150mm Hg systolic and 90mm Hg diastolic. In addition, repeated doses of cocaine will not be administered (and the study physician will halt continued cocaine delivery) if there are behavioral manifestations of cocaine toxicity (agitation, psychosis, inability to cooperate with study procedures).   Stopping Criteria for Further Participation Subject participation will be terminated if any of the following events occur: 1. Systolic BP above 180 mm Hg sustained for 5 minutes or more; 2. Diastolic BP above 120 mm Hg sustained for 5 minutes or more; 3. Heart rate above (220 – age x 0.85) bpm sustained for 5 minutes or more. Note: if a single value exceeding the values above is detected, the readings will be repeated until it is determined whether or not the stopping criteria have been met.  Adverse event assessment and management. We will assess participants’ well-being daily. Spontaneously reported symptoms or complaints will be recorded and reported to the IRB and NIDA and the FDA if events are classified as serious. Specific guidelines have been developed to guide assessment and intervention in the event of cardiovascular toxicity, such as malignant hypertension, ventricular arrhythmia, chest pain, etc., and are in use for our other studies involving cocaine administration. These guidelines are intended to support rather than supersede clinical judgment. If needed, a code team responds. Participants needing to be transferred to a medical or ICU ward can be, though this has never been necessary.   Assessments see attached | | --- | --- | | |

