| | Describe and assess any potential risks/discomforts and assess the likelihood and seriousness of such risks: | | --- | | |  | Potential risks of the study are those conferred by administration of doxazosin, administration of cocaine, and administration of the combination of the two. Other risks include those associated with residence on the research commons such as inadvertent breach of confidentiality.   Risks of Study drugs: Risks of cocaine; The risks from cocaine are raised or lowered blood pressure and heart rate, tremors, vomiting, convulsions, stroke, myocardial infarction, and in very rare instances, possibly death. If taken in high doses, cocaine can cause paranoia and delusions, but if taken in the doses used in this study, these effects are uncommon. The most frequent effects are changes in blood pressure and heart rate; the other effects are quite rare.   Risks associated with doxazosin administration; Dizziness, headache, drowsiness, lack of energy, weakness, palpitations, and nausea. In most instances side effects have disappeared with continued therapy or have been tolerated with no decrease in dose of drug. Less frequent adverse reactions which are reported to occur in 1-4% of patients are: Gastrointestinal: vomiting, diarrhea, constipation. Cardiovascular: edema, orthostatic hypotension, dyspnea, syncope. Central Nervous System: vertigo, depression, nervousness. Dermatologic: rash. Genitourinary: urinary frequency. EENT: blurred vision, reddened sclera, epistaxis, dry mouth, nasal congestion.  Risks of placebo administration; There are no known serious health risks to treatment with placebo.  Risks of Blood Collection The risks of inserting a needle into a vein may involve (1) pain from insertion of the needle; (2) lightheadedness; (3) fainting; (4) hematoma (like a bruise) at the site of the needle insertion; (5) inflammation of the vein; (6) clotting of the vein; (7) rarely, infection where the needle enters the skin, or (8) rarely, an allergic reaction to the tape applied afterwards.  Risks of ECG recording ECG recordings are safe. Some people may develop mild irritation due to the adhesive used to hold the electrodes on. The gel may also require washing your hands and chest after the study. Rarely, there may be an allergic reaction to ECG electrode adhesive, which might result in redness or swelling.  Other Risks and Discomforts   Some people get depressed after they stop using cocaine. Subjects will be monitored closely for symptoms of depression. The study team consists of psychiatrists and physicians who are all experienced in the field of drug abuse and they can provide counseling and/or medications if necessary. If subjects demonstrate severe depression, appropriate medical action will be taken to keep the subject safe. He/she may need to leave the study and will be referred to appropriate care, if they wish. No subjects with severe depressive symptomatology will be allowed to leave the hospital until it is established that they are safe (i.e., no suicidal ideation is present).  During the entry visit patients will be asked questions about their medical history and lifestyle and drug use. Some of these questions may be personal, and patients may feel uncomfortable or embarrassed. The questions will be asked in a private room such that no one besides the study staff will know the answers.  There is the risk of unauthorized disclosure of confidential information and possible unwanted encounters with friends or acqaintances in the treatment setting.  Visits to the study center for study procedures may be time consuming and inconvenient. Participation in the study will last about 28 days.  There may be risks and discomforts associated with participation in this study which are currently unforeseeable  Minimizing Risks: Subjects will be given a complete physical exam and medical history at entry to determine any reason why the study procedures should not be administered. Subjects will be instructed in the consent form and verbally to immediately report any adverse experiences that may arise. Subjectswill be instructed verbally and in the consent form to report any changes in concurrent medications and to check with their primary care physicians for any reasons they should not enter or continue on the study. Study sites will forward any and all adverse reactions information to the sponsor for analysis.  Cocaine is a strong sympathomimetic and has been associated with adverse cardiovascular events, including myocardial infarction and stroke, when taken illicitly. While these consequences have never been observed following controlled experimental administration, we will limit these potential risks in several ways: we will enroll only physically healthy subjects with no evidence of cardiovascular disease; we will administer relatively small doses of cocaine (up to 40mg); and we will monitor subjects closely in a medical hospital throughout the duration of action of the drug; and we have an intervention plan in place to deal with any adverse events that may occur.  We have extensive experience safely administering individual doses of 40mg cocaine. These doses are modest compared to amounts that participants in these studies have reported using daily; typical daily dosing patterns are on average 250mg to 500mg or more. Based on evidence from other laboratories, the risks associated with repeated cocaine administration are not substantially greater than those produced by single doses (Ward et al 1997a; Ward et al 1997b). The mechanisms that limit cardiovascular responses following repeated dosing are not known, but probably involve the development of acute tolerance to the cardiovascular effects of cocaine. We will carefully monitor participants and will not administer additional doses of cocaine until cardiovascular parameters have returned to preset limits, further safeguarding subjects. In the unlikely event that a subject experiences a medical emergency, the research commons is prepared to respond to any situation that may arise. It is located 5th floor of MEDVAC near [name] office. The general and psychiatric emergency rooms are located minutes away on the 1st floor of the hospital. There is a 24-hour medical emergency code team in the hospital. There is a 24-hour medical emergency code team in the hospital. A fully equipped crash cart is located on the unit.  It is our standard to obtain ECGs during screening, upon admission, and prior to discharge. [name] will monitor all ECGs. He has ACLS certification and has 14 years experience monitoring ECGs for studies involving cocaine administration.   Safety data will be reviewed regularly by a data and safety monitoring board. The board will be blinded to subjects' actual treatment assignments for the safety data. Reports from the DSMB will be sent to the site investigator for transmission to the appropriate IRB, in accordance with NIH policy.  Strict go/no-go criteria will be utilized for the infusions, and before and after each challenge session, subjects will be monitored using continuous heart rate, blood pressure, and EKG readings.  If suicidal ideation is identified in any subjects, the study physician will be contacted immediately and meet with the subject within one hour. If the participant expresses having a plan or has a history of previous suicide attempts, the subject will not be left alone until a study physician has met with him/her. If no physician is available 911 will be called to assess the situation. The studyphysician will determine the severity of the subject's suicidal intentions. If the study physician feels that the subject's risks are low then s/he will be given referrals to counselors, hotlines and clinics where s/he can seek further help. However, if the study physician determines that the subject's suicidal risks are high, he/she will develop a plan for safety with the subject, including but not limited to: contacting the participant's personal physician, encouraging the subjects to confide in family members or close friends,giving suicide hotline information, and providing appropriate referrals.  Sterile techniques will be utilized for blood draws and injections. Standard nursing techniques will be used to make the subjects as comfortable as possible. The entry visit interview will be administered in private with the utmost sensitivity to the subject. Prior to discharge an MD will evaluate the patients' medical (including vitals) and psychiatric status and determine if it is safe for them to be discharged. | | --- | --- | | |

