| H2.  Data and safety monitoring plan |
| | Do the study activities impart greater than minimal risk to subjects? | | --- | | |  | Yes  NOTE:  The answer to the questions in H2 requires the completion of the form: 'Section H – Data and Safety Monitoring Plan' as an attachment in Section S. | | --- | --- | | |
| H3.  Coordination of information among sites for multi-site research |
| | Is the BCM Principal Investigator acting as the SPONSOR-INVESTIGATOR for this multi-site research? | | --- | | |  | No or Not Applicable | | --- | --- | | |
| | Is BCM the COORDINATING CENTER for this multi-site research? | | --- | | |  | No or Not Applicable | | --- | --- | | |
|  |
| Section I:  Potential Benefits |
| | Describe potential benefits to be gained by the individual subject as a result of participating in the planned work. | | --- | | |  | The benefits to the participant include free testing (medical exam, lab tests, EKG) and possible discovery of reversible disease, which could be reported to a health care provider with the subjects written request and consent. There is also the opportunity to participate in research that may increase subjects' knowledge and understanding of their drug dependence and its interaction with their health status. All drug-abusing applicants for study participation will receive counseling about drug dependence and advised that treatment for drug abuse is indicated and available. Applicants not participating in the study will receive treatment referral information as appropriate. At the completion of their participation, study participants will again be advised that treatment is indicated and available, and will be given treatment referral information and assistance. In our protocols subjects are in a controlled and drug-free environment for a reasonable amount of time that oftentimes encourages them to take the first step towards either cutting down cocaine use on their own, or getting treatment. | | --- | --- | | |

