| | Describe how research population will be identified, recruitment procedures, and consent procedures in detail. | | --- | | |  | Potential subjects will be self-identified as non-treatment seeking cocaine users and recruited using advertisements in certain newspapers, on radio stations, websites, and community locations (e.g., phone booths, needle exchanges), as well as through referrals from within as well as from outside organizations, and from past research participants. Past research participants are an important source of referrals for us and they frequently ask us for business cards or other items that they can give to their friends and acquaintances. Advertisements are designed to attract cocaine users interested in participation in research on substance abuse in exchange for monetary compensation.   Recruitment will also be accomplished through referrals and word-of-mouth. Recruitment of “hidden populations” such as users of illicit drugs is difficult with standard methods such as advertisements/flyers. Though we will continue to recruit via the methods already stated, we will also use a method of recruitment called Respondent-Driven Sampling (RDS; Booth et al., 2006; Borders et al., 2008; Draus et al., 2005; Heckathorn, 2002, Wang et al., 2004). This variation of snowball samplingallows participants to serve as “seeds” for future participants, and has been found to be an effective recruitment method for “hidden populations” such as illicit drug users. Each participant will have the opportunity to refer other individuals who may be appropriate for the study. A participant who refers another individual who enrolls and completes this single-session study will receive a referral fee ($20). This fee will be processed on a monthly basis and the referring individual will receive a check within two weeks of processing. We recognize that this may result in a non-random sample. However, given the challenges of recruitment from our target population, and the significant value of obtaining discounting measures from this population, we believe this potential tradeoff is justified and appropriate. Furthermore, RDS has been found to result in sample characteristics that are stable and accurately reflect population characteristics following successful recruitment waves (Heckathorn, 2002, Wang et al., 2004).  Screening will be done by a research assistant and/or clinician and take about 2 hours to obtain informed consent, cover explanation of the study, evaluation of exclusion criteria, screening for DSM-IV criteria for MA, cocaine or other drug dependence, and administration of the intake package (see assessments section). All subjects who volunteer to participate will be adults aged 18-55, and will be judged both mentally and emotionally competent and capable of providing informed consent. This judgment will be made by study staff who are knowledgeable about and experienced in working with the drug abusing population. If there is any doubt about the decisional capacity of a potential participant, study staff will consult with the principal investigator ([name] is a clinical psychiatrist) and/or the study physician.  At several times during the consent process, participants will be informed that other forms of treatment, including abstinence-based treatment, are available and they will be referred if they so desire. The study staff will strongly encourage the subjects to take the consent home with them, review it and the study with family and/or friends, and to ask the study staff any questions they may have. After consent has been obtained, a physical and laboratory examination will include ECG and blood evaluation (chemistries, hematology). A study physician will then interview the subject for psychiatric diagnosis and review of medical data, and verify that the research subject understands the research procedures and the risk/benefit before study entry. Subjects will not be allowed to provide consent in an intoxicated state. | | --- | --- | | |

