| | Discuss the potential for psychological, social, and/or physical harm subsequent to participation in this research. Please discuss, considering the following areas: risks to privacy, confidentiality, insurability, employability, immigration status, paternity status, educational opportunities, or social stigma. | | --- | | |  | The use of patient blood for genetic testing raises special issues of confidentiality, because it is conceivable that information about patient genes could be used against patient if the wrong people knew this information. For example, an insurance company could try to deny benefits, or an employer could try to deny employment, if it became known that patient carried certain genes. To reduce this possibility, the following specific measures will be taken to protect patient confidentiality:  1. The genetic testing of patient DNA is for research purposes only. No results of genetic testing from this study will appear in the patient medical record.  2. Genetic test results will not be made available to patients or their physicians.   3. Data will be stored in a collective database kept by [name] in the Division of Addiction Psychiatry, Department of Psychiatry and Behavioral Sciences. We will store de-identified phenotypic and genotypic data in a state-of-the-art database system maintained by Baylor College of Medicine Information Technology Department. This system, called the PsychGen-DB, is a robust informatics system that integrates clinical, genetic, demographic, and security data to aid our research into the biology and genetics of psychiatric diseases. The PsychGen-DB system is a two-tiered system consisting of an Oracle back-end for data management and storage, and a web-based graphical user interface front-end application for data entry, browsing, and retrieval. The database will be accessible through an application front end within the BCM internal network. No access to the database will be granted from outside the BCM network. The application front-end uses BCMauth_appl. BCMauth_appl uses LDAP to determine a user’s access status on the BCM network. Additionally, BCMauth_appl limits users’ access based on a role assigned by the PsychGen-DB administrator. Additionally, access into PsyGen-DB database is controlled through the use of database privileges and user roles. The database administrator is responsible to administer the PsyGen-DB and will provide explicit rights only to authorized users with an authorized BCM account. The PsychGen-DB system is built on top of Oracle 10gR2. The PsychGen-DB system runs in an isolated instance of Oracle on an IBM 9117-MMA Server (64 Bit, 6 Processors Power 6 4.2GHZ, 32 GB physical memory, and AIX 5.3 operating system). This is a scalable system giving us the flexibility to grow as dictated by our needs. Contingency of our systems operations is achieved by using Hitachi Redundant Array of Independent Disk (RAID) storage. The PsychGen-DB system is backed up daily to disk using Oracle’s Recovery Manager and to a tape library system using Legato Networker Module. System administration and security patch maintenance occur once a month and is performed by a System Administrator from Baylor College of Medicine Information Technology Department. The database and application server(s) are housed in the BCM data center located at [name]. The server(s) are protected by an Uninterruptible Power Source (UPS) and backup gas generator.   While all efforts are aimed at protecting patient blood and/or DNA samples, there remains the possibility that VA could be compelled by a court or a law enforcement agency to produce such samples. We have been collecting DNA samples for years and no outside agency has ever tried to gain access to any research participant's blood or DNA samples. We believe that the risk of this happening to a patient sample is extremely small. | | --- | --- | | |

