| | **If a subject withdraws from the study:** | | --- | |
| | Will subject have the option to get the remaining portion of their sample back? | | --- | | |  | No | | --- | --- | | |
| | Will samples be destroyed? If not, will they be kept anonymously? What will happen to the sample if the subject revokes authorization? | | --- | | |  | Data obtained will be destroyed if subject revokes authorization. | | --- | --- | | |
| | Will data obtained from their sample be deleted? What will happen to the sample if the subject revokes authorization? | | --- | | |  | Data obtained will be destroyed if subject revokes authorization. | | --- | --- | | |
| | Will study data or test results be recorded in the subject's medical records? | | --- | | |  | No | | --- | --- | | |
| | Will results of specific tests and/or results of the overall study be revealed to the research subject and or his/her doctor? | | --- | | |  | no | | --- | --- | | |
| | Please identify all third parties, including the subject's physician, to receive the test results. | | --- | | |  | Results of specific tests and/or results of the overall study will NOT be revealed to the research subject or his/her doctor. | | --- | --- | | |
|  |
| **SAMPLE:  Blood** |
| | What is the purpose of the sample collection? | | --- | | |  | During screening, blood will be collected in a serum separation evacuated venous blood collection tubes (e.g., VacutainerTM) and serum separated according to standard procedures. Standard hematology and chemistry tests will be performed. | | --- | --- | | |
| | For blood draws, specify the amount drawn, in teaspoons, at each visit and across the course of the subjects entire participation time. | | --- | | |  | 2 tbls | | --- | --- | | |
| | Is there the possibility that cell lines will be developed with this sample?No | | --- | |
| | Sample will be obtained from: | | --- | | |  | Other: participant | | --- | --- | | |
| | Will the sample be stripped of identifiers? | | --- | | |  | No | | --- | --- | | |
| | **If sample will be released outside the hospital:** | | --- | |
| | Will sample be released to anyone not listed as an investigator on the protocol? Will the information be identifiable, coded or de-identified? | | --- | | |  | No | | --- | --- | | |
| | Will sample material be sold or transferred to any third parties? Will the information be de-identified? | | --- | | |  | No | | --- | --- | | |
| | **If sample will be banked for future use:** | | --- | |

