| | Where will the sample be banked and for how long? | | --- | | |  | NO | | --- | --- | | |
| | Does the banking institution have an approved policy for the distribution of samples? | | --- | | |  | n/a | | --- | --- | | |
| | **If the entire sample will NOT be used during the course of this research study:** | | --- | |
| | Will the remaining tissue be discarded? If not what will be done with the remaining sample after study completion and how long will the sample be kept? | | --- | | |  | Yes | | --- | --- | | |
| | Will samples be made available to the research subject (or his/her medical doctor) for other testing? | | --- | | |  | No | | --- | --- | | |
| | **If a subject withdraws from the study:** | | --- | |
| | Will subject have the option to get the remaining portion of their sample back? | | --- | | |  | No | | --- | --- | | |
| | Will samples be destroyed? If not, will they be kept anonymously? What will happen to the sample if the subject revokes authorization? | | --- | | |  | Yes | | --- | --- | | |
| | Will data obtained from their sample be deleted? What will happen to the sample if the subject revokes authorization? | | --- | | |  | Samples will be destroyed if subjects revokes authorization. | | --- | --- | | |
| | Will study data or test results be recorded in the subject's medical records? | | --- | | |  | No | | --- | --- | | |
| | Will results of specific tests and/or results of the overall study be revealed to the research subject and or his/her doctor? | | --- | | |  | No | | --- | --- | | |
| | Please identify all third parties, including the subject's physician, to receive the test results. | | --- | | |  | Results of specific tests and/or results of the overall study will NOT be revealed to the research subject or his/her doctor. | | --- | --- | | |
|  |
| **SAMPLE:  Sputum** |

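### The Section N Blood entry withholds screening laboratory results from participant and doctor without exception, which conflicts with the testing benefit claimed in Section I

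*Protocol*

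**What the plan says.** Section N of the protocol has a separate entry for each type of sample. The Blood entry has one stated purpose, screening: "Standard hematology and chemistry tests will be performed". It answers no when asked whether results of specific tests will be revealed to the subject or the doctor. When asked to name third parties who receive results, the subject's physician included, it replies: "Results of specific tests and/or results of the overall study will NOT be revealed to the research subject or his/her doctor". It also answers no to recording results in the medical record.

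Section I, on potential benefits, begins: "The benefits to the participant include free testing (medical exam, lab tests, EKG", with the bracket closing there. It goes on to "possible discovery of reversible disease, which could be reported to a health care provider with the subjects written request and consent".

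Section M limits its own rule to one kind of result: "Genetic test results will not be made available to patients or their physicians".

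The Urine entry in Section N includes an on-site pregnancy test and also answers no to revealing results to the subject or the doctor.

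**The concern.** The same laboratory tests are presented as a benefit in one section and closed to the participant and the doctor in another. Anyone applying Section N as written would keep a clinically significant blood result from the person it belongs to, and would refuse the report to a provider that Section I holds out.

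The eligibility rules make such results plausible. Inclusion criterion 6 in Section F1 admits liver tests above normal as long as they are below 3 times the upper limit. Exclusion criterion 6 turns away people with untreated or unstable renal or hepatic illness, for whom the result may matter most. For people who do not go on to participate, the Screening text in Section F2 offers only this: "Applicants not participating in the study will receive treatment referral information as appropriate". Section E1 classes the study as having no prospect of direct benefit to the individual, so the free testing is one of the few personal benefits that Section I can offer.

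**Working it through.** No figure in the plan is in question and no arithmetic applies. The check is a comparison of text.

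1. **Do the two sections concern the same tests?** Section I names laboratory tests. The clinical blood tests that the protocol describes are the screening hematology and chemistry (Section F2, Screening; Section J2; Section N, Blood). So the laboratory part of the Section I benefit falls under the Blood entry's disclosure rule.

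2. **The doctor.** Section I allows a report to a health care provider if the subject asks and consents in writing. The Blood entry answers a question that expressly includes the subject's physician, and it rules the doctor out without qualification. On the wording alone, these conflict directly.

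3. **The participant.** Section I does not say in terms that the participant is told the result. The conflict follows by implication: a person who is never told of an abnormal result gains nothing from the test and has no reason to make the written request. Section J2 has the nearest text: "A study physician will then interview the subject for psychiatric diagnosis and review of medical data". It provides for review by a physician and for checking that the subject understands the procedures and the risk/benefit. It does not say that laboratory results are passed on, and no other section says so.

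4. **Is there a reason to withhold?** For genetic results there is: Section M sets out the risks of disclosure, and its rule agrees with the DNA sample entry in Section N. For routine blood work the protocol gives no such reason. Section K limits who has access to research data, but gives no ground for keeping a result from the participant or from a provider the participant names in writing. The blood sample keeps its identifiers, so disclosure is feasible.

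5. **Is Blood the only entry affected?** No. All four sample entries answer no to revealing results to the subject or the doctor. Most of these answers are reasonable: the DNA results fall under Section M, and the saliva and urine assays at the outside laboratory are de-identified. The exception is the on-site urine pregnancy test. Exclusion criterion 8 in Section F1 requires that test before entry, at admission and at the end of participation. It is a clinical result under the same blanket no.

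**The case against.** The strongest reply is that the two sections can be reconciled. The Blood entry answers a template question about routine release, and Section I adds a specific exception when the subject asks in writing. The medical examination and EKG in Section I are not governed by the Blood entry, so part of the stated benefit survives in any case. This reading is possible for the doctor. It fails to settle the matter because the Blood entry states no exception, and because it leaves open how the participant would come to know there was anything to request.

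A second reply is that the Section N answers were probably not meant literally. The Urine entry plans to ask subjects for a release so that staff can follow the outcome of a pregnancy, which presupposes that the subject knows of it. This stands as evidence about intent, and it weakens any claim that results would be withheld in practice. It also shows that the written answers need correcting in more than one place.

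A third reply is that the consent form may tell participants about their laboratory results. That stands too. The form is not in the copy reviewed, so what participants are told cannot be judged.

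Some stronger readings are tempting but not supported:

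- A reader might infer that the genetic non-disclosure sentence was copied into the Blood entry, since the DNA and Blood entries share it while the Sputum and Urine entries answer none. With the same no in all four entries, this is a difference of wording and does not show that Blood is the odd one out.
- A reader might infer that the rule undermines a safety step in Section H1, which tells subjects "to check with their primary care physicians for any reasons they should not enter or continue on the study". That advice neither mentions nor depends on the study's laboratory results.

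**Conclusion.** The conflict is real and minor. The Blood entry states a rule without exception that does not fit the benefit claimed in Section I, and no section says that a participant is told of a significant laboratory result. It should be corrected as a matter of participant protection. It does not affect the design, the eligibility rules, the dosing rules or the analysis.

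Its size cannot be given, because the protocol does not state how many people are expected to have abnormal results. A reader might take the numbers in Section G1 as a measure of harm: 200 consented less 30 enrolled leaves 170. That is only a ceiling on the non-enrolled people who might have blood drawn. The true number could be as low as 0, because the draw follows the initial screening assessments, and neither figure says anything about abnormal results.

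A reader might also infer that staff would in fact withhold results. The documents do not show this: the study physician reviews the medical data and may well pass on what matters. The conclusion rests on the wording of the protocol as it stands, and on the assumption that no other study document already overrides the Blood entry.

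**What to change.** In the Section N Blood entry, replace the two non-disclosure answers with wording to this effect: the study physician tells the participant, including anyone who fails screening, of clinically significant hematology or chemistry results, and reports them to the participant's health care provider on written request and consent, as in Section I.

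Give the on-site urine pregnancy result the same exception in the Urine entry. Keep non-disclosure for genetic results and for the de-identified saliva and urine assays at the outside laboratory. The answer on the medical record can stay as it is. Check that the consent form agrees.

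The cost is two form answers in the Blood entry, one exception in the Urine entry, and a little physician time to pass on significant results. No test is added.
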